### Randomization and blinding

Eligible participants are randomly assigned to the intervention or to the control arm by using a permuted block randomization strategy to maintain reasonably good balance among groups. Blocks of four with equal number of As (intervention) and Bs (control) will be used, with the order of interventions within the block being randomly permuted (1 = AABB, 2 = ABAB, 3 = ABBA, 4 = BAAB, 5 = BABA, 6 = BBAA). Baseline characteristics of individuals randomized to each condition will be compared to verify if the randomization was successful. Health professionals referring the participants to the study platform are not aware of the randomization sequence, and even if they were, they could not control the participants’ allocation as they could not predict the sequence status at the time of the participants’ access to the study platform. Similarly, the researcher assigning the participants to each arm has no control over the order of enrolment (i.e. over who will access the online platform and when), and differs from the researcher performing the statistical analysis at a subsequent stage. The data analyst will be blinded to the intervention assigned to the participants. The study is single-blinded: participants are not unaware of the intervention received as they are active parts of the intervention. Data collection at baseline and outcome assessments are carried out in a computerized manner via study platform and resorting to self-administered instruments, thus the researcher has no influence over the measurements.

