#### Outcomes

The outcomes of this study have been widely used in intervention studies assessing the effectiveness of internet-based support tools [27]. The primary outcome is caregiver burden measured with the Zarit Burden Interview (ZBI), Portuguese validated version [48, 49], total score, at *t*_1_. The instrument comprises 22 items answered on a 5-point scale, ranging from 0 (never) to 4 (almost always) except for the final question on global burden, rated from 0 (not at all) to 4 (extremely). Total score for the ZBI ranges from 0 to 88 points, with higher scores indicating greater burden. The ZBI has good internal consistency (e.g. α = 0.89 in [55]), test-retest and interrater reliability as well as construct and concurrent validity, including reports of positive correlation with depression symptoms and time devoted to care provision [56, 57]. Regarding the psychometric properties of ZBI in Portugal, face, content, ecological, discriminant and convergent validity were documented, along with test-retest reliability (ICC = 0.93, CI95% 0.88–0.96, *p* < 0.001) and internal consistency (*α* = 0.88) [57]. The ZBI is one of the most used instruments to measure burden in intervention studies with caregivers [18].

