### Sample size calculation

As a baseline for estimating the sample size, the primary null hypothesis was stated:*H0: The change in mean caregiver burden from baseline at t*_1_
*is the same in informal caregivers of people with dementia assigned to the iSupport program as in those assigned to a minimal education-only intervention.*

A two-sided alternative hypothesis was assumed:*H1: The change in mean caregiver burden from baseline at t*_1_
*is different in informal caregivers of people with dementia assigned to the iSupport program as in those assigned to a minimal education-only intervention.*

Caregiver burden at *t*_1_ (measured with the ZBI) is the primary outcome measure, therefore used for the sample size calculation. The effect size was defined taking into account a meta-analysis reporting a mean standardized effect size of 0.65 (95% confidence interval [0.46–0.84]), for multicomponent interventions, on caregiver burden [18]. Assuming a smaller but still moderate standardized effect size of 0.5 (E/S), equivalent to about a 6-point endpoint mean difference, and a SD of 12 based on Bachner and Rourke [63] and assuming an *α* (two-sided) = 0.05 and a β = 0.2, a sample size of 64 per group was calculated as follows:

*Standardized effect size (E/S) = 6 ÷ 12 = 0.5.*

16 ÷ (standardized effect size)^2^ = 16 ÷ 0.25 = 64

Conservatively allowing for a larger dropout rate of 30% found in the literature for these interventions [47], a total of 92 informal caregivers per group was calculated:

16 ÷ 0.25 × 1.43 = 92

With a sample size of 92 per group and a dropout rate no larger than 30%, the study will be able to detect an intervention effect of 0.5 for the primary outcome.

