### Statistical analysis

Descriptive statistics will be used to characterize the IC enrolled in the intervention study: means and standard deviations for the continuous variables presenting normal distribution; medians and percentiles for continuous variables not normally distributed or ordinal variables; frequencies for nominal variables. At *t*_0_, the randomization success will be examined by comparing the characteristics of participants in both arms with the adequate statistical methods. Since the outcomes are continuous variables the best measure is the change in the outcome over the course of the study: this approach usually minimizes the outcome variability between participants and offers more power than just comparing values at the end of the study. To evaluate differences between the outcomes of each group, paired t-tests will be conducted and estimates of effect sizes calculated. All *p* values are two-sided with a significance level of 0.05. Multiple regression analyses can be used to correct for possible confounders. Generalized estimated equations (GEE) analysis can be used to examine the maintenance of the intervention effectiveness. The data will be analyzed by a researcher blinded to the group assignment.

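### Change from baseline is preferred for power with no adjustment for baseline ZBI, while the sizing rests on an endpoint SD; ANCOVA on baseline ZBI is at least as precise at any correlation

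*Protocol article*

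**What the plan says.** Four parts of the protocol article bear on the primary comparison.

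- **Outcomes:** "The primary outcome is caregiver burden measured with the Zarit Burden Interview (ZBI), Portuguese validated version", taken as the total score at t1 (3 months).
- **Sample size calculation, hypotheses:** H0 and H1 are written on change. They begin "The change in mean caregiver burden from baseline at t" and refer to t1.
- **Sample size calculation, figures:** the standardized effect of 0.5 is described as "equivalent to about a 6-point endpoint mean difference, and a SD of 12". With two-sided alpha 0.05 and beta 0.2 this gives 64 per group, raised to 92 for 30% dropout. No SD of change and no correlation between t0 and t1 is given.
- **Statistical analysis:** change over the study is put forward as the measure to prefer because "this approach usually minimizes the outcome variability between participants and offers more power than just comparing values at the end of the study". Multiple regression is optional and aimed at confounders that are not named. Baseline ZBI is not named as an adjustment variable there, nor does it appear in the Covariates section.

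**The concern.** The hypothesis and the analysis rationale concern change, while the sizing uses the SD of a single score. These agree only under a particular correlation between the two visits, which the article does not state. The reader therefore cannot tell what power the planned analysis has.

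The rationale also compares change only with an unadjusted comparison of end values. It leaves out the usual third option, an end-value comparison adjusted for baseline, which uses the same data and does not lose precision when the correlation is low.

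Precision matters here by the article's own account. Its Discussion says that burden measured by the ZBI may respond weakly to intervention, that recruitment carries most of the study's risk, and that high dropout is expected.

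**Working it through.** **Inputs from the article.** Difference 6 points, SD 12, two-sided alpha 0.05, power 0.80, and 30% dropout (Sample size calculation). Allocation is 1:1: "Blocks of four with equal number of As (intervention) and Bs (control) will be used" (Randomization and blinding).

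**Assumptions.** The correlation r between t0 and t1 ZBI is not given, so it is varied. The table takes SD 12 at both visits.

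**1. The plan's own figures.** 16 ÷ 0.5² = 64 per group. A two-sample t-test calculation gives 63.8, so 64. With dropout, 64 ÷ 0.70 = 91.4, so 92 (the article's 64 × 1.43 = 91.5 also rounds to 92). Power at 64 per group is 0.801 by the t-test and 0.807 by the normal approximation. The stated figures reproduce for an endpoint comparison.

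**2. Standard deviations of the three analyses.**

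- Endpoint: 12
- Change: 12 × √(2(1 − r))
- ANCOVA residual: 12 × √(1 − r²)

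**3. Power at 64 evaluable per group for 6 points.** Normal approximation: Φ(6 ÷ (SD × √(2/64)) − 1.96). For change at r = 0.3: 6 ÷ (14.20 × 0.1768) − 1.96 = 0.43, so 0.667; the t-test gives 0.660.

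| r (assumed) | SD change | SD ANCOVA | Power, change (t-test) | Power, endpoint (t-test) | Power, ANCOVA (normal approx.) |
|---|---|---|---|---|---|
| 0.3 | 14.20 | 11.45 | 0.660 | 0.801 | 0.843 |
| 0.5 | 12.00 | 10.39 | 0.801 | 0.801 | 0.904 |
| 0.7 | 9.30 | 8.57 | 0.952 | 0.801 | 0.977 |

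A simulation of 20,000 trials per r agrees. Change gave 0.663, 0.800 and 0.953; ANCOVA gave 0.836, 0.899 and 0.975.

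**4. Evaluable participants per group for 80% power (normal approximation).** Change against ANCOVA: 88 against 58 at r = 0.3, 63 against 48 at r = 0.5, 38 against 33 at r = 0.7. With equal SDs the ratio is (1 − r²) ÷ (2(1 − r)) = (1 + r)/2, that is 0.65, 0.75 and 0.85.

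**5. The ranking without equal SDs.** Let SD0 and SD1 be the SDs at t0 and t1.

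- Var(change) − Var(ANCOVA residual) = SD0² + SD1² − 2r·SD0·SD1 − SD1²(1 − r²) = (SD0 − r·SD1)², never negative.
- Var(endpoint) − Var(ANCOVA residual) = r²·SD1², never negative.
- Change beats endpoint only if r > SD0 ÷ (2·SD1), which is 0.5 when the SDs are equal.

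ANCOVA spends one degree of freedom on the slope. At r = 0, where it has nothing to gain, simulated power was 0.797 against 0.799 for the endpoint comparison.

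**The case against.** **The sentence is hedged.** It says that change usually gains power, and compares it only with end values. That is true with equal SDs whenever r exceeds 0.5. This stands: the sentence is not false. What remains overstated is ranking change as the preferred measure without considering baseline adjustment.

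**No low correlation is shown.** A reader might infer that the trial is underpowered, or that 80% power is known to fail. The article does not support that. Its only repeat-measure figure is a ZBI test-retest ICC of 0.93 (95% CI 0.88 to 0.96, Outcomes). That is not a 3-month correlation in this trial, but it points upward. If r exceeds 0.5 with equal SDs, 64 per arm is conservative for change as well.

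**Eligibility does not supply the missing evidence.** It is tempting to argue that selecting burdened carers narrows the baseline range, lowers r and so costs power. Narrowing also lowers SD0, and with it the break-even SD0 ÷ (2·SD1). Take an assumed example with r = 0.5 and SD 12 before selection, and baseline variance halved from 144 to 72. The slope is 0.5 and the residual variance 108. Var(change) is then 108 + 0.25 × 72 = 126, an SD of 11.2, smaller than 12 although r falls to 0.38. Entry is also possible through the anxiety or depression score alone, so low ZBI scores are not excluded.

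**The three wordings are not three effects.** Under randomisation, the between-arm differences in t1 mean, in mean change and in baseline-adjusted mean all target the same quantity. This stands: the mismatch is one of wording and precision, not of bias.

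**An article may leave covariates to a fuller document.** This is true of detail. Here, however, the article itself states the hypothesis, the sizing and the reason for the analysis, and these can be compared as printed.

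**Conclusion.** The point holds as an efficiency improvement that should be made, not as a demonstrated error. The 64 and 92 per arm are correct for an endpoint comparison with SD 12. Power for the change-score analysis rests on an unstated correlation and could lie on either side of 80%; the article does not show which.

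The advantage of ANCOVA does not depend on that unknown. At 64 per arm with equal SDs it adds about 18 percentage points over change at r = 0.3, 10 at r = 0.5 and 2 to 3 at r = 0.7. It also corrects for chance baseline imbalance in ZBI. The power figures assume a 6-point difference, SD 12 at both visits and 64 evaluable per arm. The ranking of the variances needs no assumption about r or equal SDs, apart from the negligible lost degree of freedom.

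**What to change.** 1. In Statistical analysis, name one primary analysis: the between-arm comparison of t1 ZBI by ANCOVA with baseline ZBI as covariate.
2. Replace the rationale for change scores with a sentence saying that baseline adjustment is at least as precise as either a change or an endpoint comparison.
3. In Sample size calculation, state that 64 per arm rests on an endpoint SD of 12 and is therefore conservative for ANCOVA.
4. Use the same description of the primary comparison in Outcomes, in H0 and H1, and in Statistical analysis.

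The cost is wording only. No participants or assessments are added, since the ZBI is completed at screening and serves as the baseline measure. Naming one model also removes any later choice between endpoint, change and adjusted results.

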### Variables and data collection methods

Data collection will be carried out at three different time points: i. at baseline (*t*_0_); ii. post-intervention (3 months after baseline; *t*_1_); and iii. follow-up (6 months after baseline; *t*_2_). Table 1 presents the schedule of interventions and assessments. Primary and secondary outcomes are measured through self-report instruments composing the data collection protocol. All data will be collected in a computerized manner through the study online platform. Three and six months after the baseline (*t*_1_ and *t*_2_), the participants are invited by email to fill in the online questionnaires and, as an attempt to avoid missing data, two reminders are foreseen for each assessment (see Fig. 1).

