The data analysis will follow an Intention-to-treat (ITT) protocol, therefore participants will be analyzed as randomized. This approach is an important protection against bias by preserving the randomization benefits, in particular by balancing known and unknown factors and eliminating selection bias. As the ITT approach requires either no attrition or a strategy to handle missing data, to minimize the first, reminders for both assessments (*t*_1_ and *t*_2_) are foreseen and to address the second, missing data on follow-up measurements will be imputed using multiple imputations. In addition, a per protocol sensitivity analysis will be conducted to ‘bracket’ the likely effects under different conditions. For this purpose, a minimum number of completed lessons (*n* = 5), in addition to the completion of the assessments (*t*_1_ and *t*_2_), will be considered. An interim analysis is foreseen, to be implemented before the participants’ enrolment is completed. As the intervention study does not raise relevant concerns about intervention safety, a single look/interim assessment, when half of the sample is reached, is planned. Elements to monitor in the interim analysis include recruitment, adherence to intervention, follow-up completeness, and reported harms. Measures that might arise from the interim analysis include extending the study in time, increasing the study sample or stopping the study. The study should be stopped in case of determination of benefit or harm, or in case of being identified a negligible chance of demonstrating effectiveness if the intended number of participants were fully enrolled. Only the research team will have access to the interim results and make the final decision to terminate the trial if fulfilled the stopping criteria. To minimize type I error, the *α* will be decreased in the interim analysis. All analyses will be conducted using SPSS for Windows.

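### The single per-protocol set requires the 6-month assessment as well, so the 3-month per-protocol sensitivity analysis loses participants whose primary outcome was observed

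*Protocol article*

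**What the plan says.** - **Endpoint.** Outcomes: "The primary outcome is caregiver burden measured with the Zarit Burden Interview (ZBI), Portuguese validated version [48, 49], total score, at *t*_1". Sample size calculation: both hypotheses concern the change from baseline at t1, and burden at t1 "is the primary outcome measure, therefore used for the sample size calculation".
- **Timing.** Variables and data collection methods lists "post-intervention (3 months after baseline; *t*_1" and "follow-up (6 months after baseline; *t*_2". Access to iSupport lasts 3 months, so it ends at about t1.
- **Main analysis.** Statistical analysis: participants are analysed as randomised, and missing follow-up scores are multiply imputed.
- **Sensitivity analysis.** Same section: "a per protocol sensitivity analysis will be conducted to ‘bracket’ the likely effects under different conditions". The set is defined by "a minimum number of completed lessons (*n* = 5") and, "in addition to the completion of the assessments (*t*_1_ and *t*_2_), will be considered". No other per-protocol set is described, and the definition is not restricted to the 6-month analyses.

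**The concern.** The assessment condition does not fit the endpoint that the trial is built on. Someone who completed the lessons and answered the ZBI at 3 months has everything that the t1 contrast needs. Missing the 6-month questionnaire is not a departure in exposure during the 3-month access period, nor in the measurement of the 3-month outcome. It happens after that outcome is fixed, and the outcome may influence it.

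What is at stake is how the sensitivity analysis can be read. It is meant to show how the estimate moves when adherence is taken into account. With the t2 condition in place, a difference from the ITT result mixes lesson exposure with retention after the outcome, and the two cannot be separated. Precision is also lost with nothing gained for the t1 question.

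**Working it through.** **Plan's own figures** (Sample size calculation: 6-point difference, SD 12, two-sided 0.05, power 0.80, 30% dropout).
- Standardised effect 6 / 12 = 0.5. Per group 16 / 0.5² = 64.
- Inflated: 64 × 1.43 = 91.5, rounded up to 92 (64 / 0.70 = 91.4 gives the same).
- Both figures reproduce, and the point raised here does not change them.

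**Tracing one participant through the rule.** Five or more lessons: met. ZBI at t1: observed. Questionnaire at t2: not returned. Result: in the ITT analysis with the observed t1 score, but out of the only per-protocol set, including for the t1 contrast.

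**How many.** The article does not say when the 30% dropout occurs, so two assumed ranges are shown. Both look at the assessment condition alone, before the lesson criterion.

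*Range A: 30% of those randomised are missing by t2, and 10% to 20% of those randomised are already missing at t1.* With both assessments: 92 × 0.70 = 64.4 per arm.

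| Missing at t1 | With t1 | Dropped by t2 rule | Share of observed t1 | Variance ratio |
|---|---|---|---|---|
| 10% | 82.8 | 18.4 | 22% | 82.8 / 64.4 = 1.29 |
| 15% | 78.2 | 13.8 | 18% | 78.2 / 64.4 = 1.21 |
| 20% | 73.6 | 9.2 | 12.5% | 73.6 / 64.4 = 1.14 |

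The variance ratio needs only the counts. To put it in ZBI points, assume a t0–t1 correlation of 0.6 (not in the article). The SD of change is 12 × √(2 × (1 − 0.6)) = 10.7, and the SE is 10.7 × √(2 / n). That gives 1.67 to 1.77 with everyone observed at t1, and 1.89 with the t2 rule. Power for a standardised effect of 0.5 (normal approximation) is 0.81 with the rule, against 0.90 to 0.86 without it.

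*Range B: 30% are already missing at t1 (64 per arm observed), and a further 5% to 20% of those miss t2.*

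| Further loss | Dropped by t2 rule | Left per arm | Power for 0.5 |
|---|---|---|---|
| none | 0 | 64 | 0.81 |
| 5% | 3.2 | 60.8 | 0.79 |
| 10% | 6.4 | 57.6 | 0.77 |
| 15% | 9.6 | 54.4 | 0.74 |
| 20% | 12.8 | 51.2 | 0.72 |

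**Bias, as illustration only.** Take range A, with t2 non-response among t1 responders logistic in the t1 change score and calibrated to 30% missing by t2. If worse change doubles the odds of missing t2 per SD in the iSupport arm only, the t1 contrast moves 0.9 to 1.5 points towards iSupport. With an odds ratio of 3 it moves 1.3 to 2.2 points. With the same loss and the same odds ratio in both arms, the shifts cancel and the bias is zero.

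**The case against.** - **The article does not contradict itself.** This stands. One might infer that it sets two follow-up rules for the same endpoint, but the endpoint is fixed in one place and the sensitivity set in another, and that set is not tied to one outcome. A common set of those who completed both follow-ups is a recognised choice and keeps the same people at both time points. The criticism is that the set suits the t1 contrast badly.
- **The wording is loose, and analysis sets are usually detailed in the analysis plan.** Partly right: saying that completion will be considered is not firm. But both time points are named, and this is the only definition offered. The point concerns a rule that is stated, not detail that is absent.
- **The main result is untouched.** This stands and sets the severity. One might infer that observed primary outcomes are lost to the trial, but the ITT analysis keeps all of them. Any per-protocol set selects after randomisation, and the lesson criterion already does. The t2 condition adds selection that the t1 question does not need.
- **The figures are assumptions.** This stands. The sample size section links the 30% to detecting the effect on the primary outcome, which fits range B at least as well as range A. In range A the 64 left per arm equal the designed evaluable number, so the loss there is relative to a surplus.
- **Bias is not demonstrated.** This stands. One might infer that the t1 per-protocol estimate will favour iSupport, but nothing in the article supports a link between t1 burden and t2 non-response that differs by arm, nor its size or direction.

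**Conclusion.** The point holds in limited form. As written, the per-protocol set excludes caregivers with an observed 3-month score because of later non-response. That makes the t1 sensitivity analysis less precise and adds avoidable selection on a post-outcome event, so its gap from the ITT result cannot be attributed to exposure alone.

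The loss is about 9 to 18 observed t1 outcomes per arm under range A and about 3 to 13 under range B. Both rest on an assumed split of dropout between t1 and t2, and both are taken before the lesson criterion. Bias would require t2 non-response to depend on t1 burden differently in the two arms, which is possible but not shown. The sample size, the primary estimate and the primary inference are unaffected. Severity is minor; this is a cheap improvement.

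**What to change.** In Statistical analysis, tie the assessment condition to the endpoint. For t1 outcomes, including the primary one, the per-protocol set requires completion of t0 and t1. Completion of t2 is required only for per-protocol analyses of t2 outcomes. Report the size of both sets by arm.

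The cost is one sentence, settled before the data are analysed, with no extra data or participants. The downside is that the t1 and t2 per-protocol sets will contain slightly different people, so the two results are not a strict comparison over time within one group. Reporting both set sizes makes that visible.
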